## Abstract

**Background:**

Acute kidney injury (AKI) is a common complication of cardiac surgery. Factors such as cardiopulmonary bypass, aortic cross-clamping and surgical stress may precipitate renal hypoperfusion and ischaemia, inflammation and oxidative stress are associated with development of AKI. Albumin’s pharmacological properties and widespread availability have the potential to mitigate these factors. However, the effect of albumin on cardiac surgery-associated AKI is unknown.

**Objective:**

To evaluate the impact of postoperative 20% albumin infusion on kidney function after high-risk cardiac surgery.

**Methods:**

We designed an open-label, multicentre, randomised controlled trial—the ALBICS study (ALBumin Infusion and acute kidney injury following Cardiac Surgery). A total of 590 patients undergoing high-risk cardiac surgery (combined procedure or estimated glomerular filtration rate (eGFR) < 60 mL/min/1.73 m^2^) will be enrolled into the study and randomly allocated to receive a postoperative 20% albumin infusion or standard care in a 1:1 ratio, stratified by centre and baseline renal function. The study fluid will be administered upon arrival in intensive care for 15 h. Patients will be followed up until 28 days after surgery or until discharge from the hospital. The primary outcome is the proportion of patients who develop AKI in both groups. Secondary outcomes to be measured are proportions of AKI stage II and III, 28-day mortality, mechanical ventilation time and length of stay in intensive care and hospital.

**Conclusion:**

This trial aims to determine if a postoperative infusion of concentrated albumin reduces the risk of AKI following high-risk cardiac surgery.

**Trial registration:**

Australian New Zealand Clinical Trials Registry ACTRN12619001355167. Registered on 03 October 2019—retrospectively registered. https://www.anzctr.org.au/Trial/Registration/TrialReview.aspx?id=378383.

## Administrative information

The order of the items has been modified to group similar items (see http://www.equator-network.org/reporting-guidelines/spirit-2013-statement-defining-standard-protocol-items-for-clinical-trials/

## Background and rationale {6a}

Acute kidney injury is a well-recognised complication of cardiac surgery (CSA-AKI). A large retrospective cohort study of 25,086 patients reported CSA-AKI in 30% of patients [1]. This study also demonstrated odds ratios of in-hospital mortality equal to 3.17 in Acute Kidney Injury Network (AKIN) stage 1 and 43.77 in AKIN stage 3. Given that over one million patients undergo cardiac surgery each year, CSA-AKI presents a significant burden of disease [2].

### Pathophysiology and risk factors

Current understanding of the pathophysiological mechanisms surrounding CSA-AKI are limited. There is unlikely to be a single mechanism responsible for AKI in these patients but instead a myriad of injurious pathways that take place in the perioperative period. Many of these pathways relate to renal perfusion, inflammation and oxidative stress (Fig. 1).

**Fig. 1 Fig1:**
[figure not shown]
Pathophysiology of CSA-AKI

Cardiopulmonary bypass (CPB) is associated with postoperative renal injury, likely via a reduction in renal blood flow and glomerular filtration [3]. Non-pulsatile flow may also result in an imbalance between cortical and medullary perfusion [4]. Haemodilution is an inevitable consequence of CPB and has been identified as an independent predictor of CSA-AKI [5–7]. The renal medulla and corticomedullary junction are particularly vulnerable to these changes given their relative hypoxia in comparison to other tissues [8, 9]. Prolonged hypoperfusion precipitates ischaemic changes such as inflammatory cell infiltration, cell contraction and necrosis [10]. Other operative risk factors include aortic cross-clamp time, blood transfusion, inotrope requirements and the complexity of the procedure performed [11, 12].

Cardiac surgery results in increased levels of pro-inflammatory cytokines, notably interleukin (IL)-6 and tumour necrosis factor (TNF)-α [13] with increased risk of AKI after cardiac surgery [14–16]. Subsequent activation of macrophages, neutrophils and lymphocytes lead to renal parenchymal infiltration and development of AKI [17, 18].

### Hypoalbuminaemia and cardiac surgery

Hypoalbuminaemia is common after cardiac surgery. A large observational study (*n* = 2818) found that 94% of patients with normal preoperative serum albumin levels developed hypoalbuminaemia at 24 h after cardiac surgery, where the risk of AKI approximately doubled with each 5 g/l reduction [19].

In separate meta-analyses of 90 cohort studies and 9 RCTs totalling 291,433 and 535 acutely ill patients, Vincent et al. found that a 10 g/l reduction in serum albumin correlated with an increased odds of mortality and morbidity of 116% and 52% after cardiac surgery [20]. The analysis of randomised trials also suggests that albumin supplementation to maintain serum levels greater than 30 g/l decreases the rate of complications. These results contend that hypoalbuminaemia is common after cardiac surgery and its correction may prevent AKI.

Albumin administration may not be useful in all critically ill populations. A recently published randomised trial of 828 hypoalbuminaemic patients with acute complications of decompensated cirrhosis randomised patients to receive daily 20% albumin infusions titrated to the degree of hypoalbuminaemia [21]. Despite increasing serum albumin concentrations, albumin administration failed to improve outcomes with respect to in-hospital kidney dysfunction and mortality at 28 days, 3 months and 6 months.

### Nephroprotective properties of albumin

Albumin may have nephroprotective effects via different mechanisms. Albumin infusion reduces fluid overload which is an independent risk factor for AKI in critically ill patients [22–24]. A rise in venous pressure and subsequent renal interstitial oedema impair glomerular filtration [25] and may reduce cortical oxygen pressures [26].

The HAS FLAIR trial found similar results comparing 20% albumin and crystalloid fluid bolus therapy over the first 24 h after cardiac surgery (median 1100 ml vs 1970 ml, *p* = 0.001, *n* = 100) [27]. Additionally, the SWIPE trial found that in a sample of 321 ICU patients, half of whom had undergone cardiac surgery, 20–25% albumin preparations reduced fluid requirements in the first 48 h compared to 4–5% albumin preparations (median 3429 ml vs 4217 ml, *p* = 0.06) [28].

Injury to the endothelium contributes to the development of AKI. Endothelial damage increases leukocyte adherence, platelet aggregation, vasoconstriction and podocyte dysfunction [29]. Loss of the glycocalyx is thought to relate to microthrombi, ischaemia reperfusion injury, oxidative stress and systemic inflammation; all of which may occur following CPB [10, 30, 31]. Administration of albumin protects the glycocalyx. In animal models, administration of albumin resulted in reduced measures of glycocalyx dysfunction [32, 33].

Albumin contributes to antioxidant activity in plasma. Over 70% of free radical neutralisation is attributable to albumin [34]. This property is predominantly due to its abundance and the existence of a thiol group in the cysteine-34 position of its molecular structure. Thiols are known for their reaction with, and ‘trapping’ of, reactive oxygen species. In healthy subjects, 70–80% of serum albumin is reduced at the cysteine-34 thiol, while an additional 25% may be oxidised further [35, 36].

### Clinical trials of albumin and cardiac surgery

In the first and only clinical trial investigating albumin in this way, Lee et al. randomised 220 patients with undergoing off-pump cardiac surgery to receive either preoperative 20% albumin or saline [37]. This double-blind study included patients with preoperative serum albumin level less than 40 g/l. The volume of fluid administered varied between 100 and 300 ml and was titrated to each patient’s preoperative serum albumin level. Albeit limitations, the trial reported reduced risk of AKI by Kidney Disease: Improving Global Outcomes (KDIGO) [38] (RR = 0.533, *p* = 0.048) and Acute Kidney Injury Network (AKIN) criteria (RR = 0.557, *p* = 0.031) with albumin administration.

There is insufficient scientific literature to determine the utility of exogenous albumin to prevent CSA-AKI. More clinical trials are needed in this area.

## Objectives {7}

We hypothesise that an infusion of 20% albumin will reduce the proportion of patients who develop postoperative AKI after high-risk cardiac surgery, when compared to standard care.

The objective of this study is to evaluate the impact of postoperative 20% albumin infusion on kidney function after high-risk cardiac surgery.

## Trial design {8}

The ALBICS (ALBumin Infusion and acute kidney injury following Cardiac Surgery) study is a multicentre, parallel-group, open-label, prospective, randomised controlled, superiority trial.

### Methods: participants, interventions and outcomes

#### Study setting {9}

Patients will be recruited at the following Australian hospitals: Monash Medical Centre, Cabrini Hospital, University Hospital Geelong, Prince of Wales Hospital, Prince of Wales Private Hospital and the Austin Hospital.

#### Eligibility criteria {10}

To be included in the study, patients must meet all of the following inclusion criteria:
Aged 18 years or older;Have undergone cardiac surgery;At least one of the following:
i.Estimated glomerular filtration rate (eGFR) < 60 mL/min/1.73 m^2^, orii.Have had a combined valve and coronary procedure, oriii.Two or more valve procedures, oriv.Surgery involving the thoracic aorta.

Patients meeting any of the following exclusion criteria will be excluded from the study:
eGFR < 15 mL/min/1.73 m^2^,Serum albumin < 20 g/l,Dialysis dependence,Kidney transplant,Undergone off-pump cardiac surgery,Requiring extra-corporeal life support or ventricular assist device immediately postoperative,Jehovah’s Witness.

#### Who will take informed consent? {26a}

A study investigator will obtain informed consent from each participant prior to enrolment in this study. The investigator will discuss the risks and benefits of participation and will check that the patient comprehends the information provided. Consent will be voluntary and free from coercion.

#### Additional consent provisions for collection and use of participant data and biological specimens {26b}

Not applicable.

## Interventions

### Explanation for the choice of comparators {6b}

Patients will be randomly allocated to either the intervention group (albumin 20% and standard care) or the comparator group (standard care only). Standard care was chosen as an appropriate comparator given that the intervention is proposed as an adjunct to routine care.

### Intervention description {11a}

Patients randomised to the intervention arm will receive an intravenous infusion of 20% albumin for 15 h at 20 ml/h as soon as possible after ICU admission, where the time to initiation of infusion does not exceed 6 h.

Patients randomised to the standard care arm will not receive any 20% albumin for the first 24 h of ICU admission.

### Relevant concomitant care permitted or prohibited during the trial {11d}

Both treatment groups will receive standard care as per the clinician in charge. This includes any background treatments considered routine care such as vasopressors, inotropes, ventilation and initiation of dialysis. Administration of 4% albumin will not be restricted.

### Criteria for discontinuing or modifying allocated interventions {11b}

For those randomised to receive 20% albumin, the infusion may be ceased if the patient develops an allergic reaction or fluid overload (shortness of breath, increased oxygen requirements).

For those randomised to receive standard care, 20% albumin may be administered within the first 24 h if it is deemed clinically indicated. These decisions will be at the discretion of the clinician in charge.

### Strategies to improve adherence to interventions {11c}

The design for the ALBICS study will be presented to staff at each participating site, with input from intensive care specialists, cardiac surgeons and cardiac anaesthetists. These meetings will improve consistency of protocol implementation. Other measures include presentations and visual information provided to clinical staff to reduce the risk of inadvertent protocol deviation.

### Provisions for post-trial care {30}

All patients enrolled in this trial will receive standard postoperative surgical care beyond 24 h. Patients will be followed as per the study protocol.

### Outcomes {12}

The primary outcome is the proportion of patients that develop AKI within hospital stay up to Day 28 post-enrolment. AKI is defined by creatinine-based KDIGO criteria (Table 1 Pathophysiology of CSA-AKI) [38]. Patients after cardiac surgery often have polyuria in the first few hours after surgery and they are frequently given diuretic therapy after day 1 postoperatively. For this reason, urine output may not a be a reliable measure of AKI.

**Table 1 Tab1:** KDIGO creatinine-based criteria for diagnosis and staging of AKI

Stage	Serum creatinine
I	1.5–1.9 times baseline within 7 days; or ≥ 26.5 μmol/l (≥ 0.3 mg/dl) increase within 48 h
II	2.0–2.9 times baseline within 7 days
III	≥ 3.0 times baseline within 7 days; or Increase to ≥ 353.6 μmol/l (≥ 40 mg/dl); or Initiation of renal replacement therapy

Secondary and tertiary outcomes are described in Table 2. These outcomes were chosen as appropriate measures of acute deterioration or recovery, and the haemodynamic effects of albumin.

**Table 2 Tab2:** Study outcomes

Primary outcome	In-hospital AKI Stage I, II or III (proportion of patients)
Secondary outcomes	In-hospital AKI stage II and III (proportion of patients) In-hospital mortality ICU LOS (hours) Hospital LOS (days) Ventilation time (hours)
Tertiary outcomes	Peak SCr (μmol/l) Serum albumin at 24 h (g/l) Serum Hb at ICU discharge (g/l) Proportion of patients needing inotrope and/or vasopressor therapy Net fluid balance at 48 h (ml) Quantity of RBCs transfused over first 48 h (ml) Initiation of CRRT

*AKI*, acute kidney injury; *CRRT*, continuous renal replacement therapy; *Hb*, haemoglobin; *ICU*, intensive care unit; *LOS*, length of stay; *RBC*, red blood cell; *SCr*, serum creatinine

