### Participant timeline {13}

Patients will be followed up until the 28th day post-enrolment or hospital discharge, whichever occurs first. Data collected will be restricted to the parameters that are necessary to define clinical characteristics and will be obtained from routine laboratory investigations and hospital records (Fig. 2). This includes baseline demographics, outcome measures, physiological parameters, operative data, therapeutic interventions, death and other adverse events.

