## Statistical methods

### Statistical methods for primary and secondary outcomes {20a}

Normality of continuous variables will be assessed and log-transformed where appropriate. Equality of variance for normally distributed variables will be assessed using Levene’s test. Between-group comparisons will be performed using chi-squared tests for equal proportion, Student’s *t* test for continuous variables with equal variance, Welch’s *t* test for continuous variables with unequal variance, and Mann-Whitney *U* test otherwise. Categorical variables will be described as frequency with proportions (%). Continuous variables will be expressed as mean ± standard deviation if normally distributed, and median with interquartile range if not normally distributed. Analysis will be performed using R version 4.0.2 (R Foundation for Statistical Computing, Vienna, Austria).

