### Methods in analysis to handle protocol non-adherence and any statistical methods to handle missing data {20c}

Data will be analysed using an intention-to-treat methodology. A per-protocol sensitivity analysis will also be conducted. Ongoing site education would reduce the risk of protocol deviation. We will adjust for missing data using multiple imputation.

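### Stay and ventilation times carry no rule for death, so if mortality differs between arms their comparison leans towards the arm with more deaths

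*Protocol article*

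**What the plan says.** Table 2 (Outcomes {12}) gives three secondary outcomes as durations, "ICU LOS (hours) Hospital LOS (days) Ventilation time (hours"). "In-hospital mortality" is a separate secondary outcome and is not combined with them. The same section presents the outcomes as measures of deterioration or recovery.

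Section {20a} sets one route for every continuous variable. It begins "Normality of continuous variables will be assessed and log-transformed where appropriate", then uses Levene's test to choose Student's t "test for continuous variables with equal variance" or Welch's t, with Mann-Whitney U "test otherwise".

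Section {20c} states "Data will be analysed using an intention-to-treat methodology", so patients who die stay in the comparison, and adds "We will adjust for missing data using multiple imputation". Section {13} limits observation: "Patients will be followed up until the 28th day post-enrolment or hospital discharge, whichever occurs first".

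No section shown gives patients who die a value or rank, restricts these comparisons to survivors, uses ventilator-free or ICU-free days, or names a method for competing events or censoring.

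**The concern.** A duration measures recovery only if it ends in recovery. A patient who dies in the ICU at 12 h and one who leaves it well at 12 h have the same observed ICU stay, and t tests and Mann-Whitney cannot tell them apart. If albumin raised or lowered early mortality, stay and ventilation time would shift in the misleading direction: the arm with more deaths would look quicker to recover.

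Two smaller matters sit beside this. A hospital stay still running at day 28 is not fully observed, yet the named tests treat every value as complete. And because the test is settled by checks on the data, the reported contrast could be a difference in means, a ratio on the log scale or a rank comparison.

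**Working it through.** **Plan's own figure.** The article gives no figure for these outcomes. Its only design calculation is for AKI, 30% versus 20%, 80% power, two-sided 0.05:

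n = [1.960·√(2·0.25·0.75) + 0.842·√(0.3·0.7 + 0.2·0.8)]² / 0.10² ≈ 294 per arm, or 588 in total against the stated 590. Power at 295 per arm is 80.2%. Nothing below changes this.

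**Inputs.** From the article: 590/2 = 295 per arm, the named tests, intention to treat, day 28. Assumed, because the article gives no values: survivors' ICU stay log-normal, median 48 h, log-SD 0.8; deaths spread evenly over 6 to 36 h; the same recovery in both arms; mortality p_C in control and p_A with albumin. Putting the extra deaths in the albumin arm is only for illustration; the result is symmetric.

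**Rank comparison.** Let q be the chance that a survivor's stay exceeds the stay of a patient who dies. The chance that a random albumin stay is longer than a random control stay is

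θ = 0.5 − (q − 0.5)(p_A − p_C).

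Here q = (1/30)∫ from 6 to 36 of [1 − Φ(ln(x/48)/0.8)] dx = 0.840. If death is ranked worst, q becomes 0 and θ = 0.5 + 0.5(p_A − p_C). So whenever q exceeds 0.5 the two versions point in opposite directions. When p_A = p_C both equal 0.5.

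**Mean.** Survivors' mean is 48·exp(0.8²/2) = 66.1 h and the mean among deaths is 21 h, so the shift is (p_A − p_C)(21 − 66.1). At 4% versus 8% that is 0.04 × (−45.1) = −1.80 h.

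**Median.** All deaths fall below the median, so it solves Φ(ln(x/48)/0.8) = (0.5 − p)/(1 − p). This gives 47.03, 46.53, 46.04 and 43.98 h at p = 2%, 3%, 4% and 8%.

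The last column is simulated: the share of trials with a significant Mann-Whitney result favouring the arm with more deaths (nominal 2.5%). Ranges are across repeated runs.

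| Deaths, control vs albumin | Median shift (h) | Mean shift (h) | θ as written | θ, death worst | Significant, wrong direction |
|---|---|---|---|---|---|
| 4% vs 4% | 0 | 0 | 0.500 | 0.500 | 2.2–2.7% |
| 2% vs 3% | −0.49 | −0.45 | 0.497 | 0.505 | about 3–4% |
| 2% vs 4% | −0.99 | −0.90 | 0.493 | 0.510 | 4.3–4.9% |
| 3% vs 6% | −1.51 | −1.35 | 0.490 | 0.515 | 6.1–6.8% |
| 4% vs 8% | −2.05 | −1.80 | 0.486 | 0.520 | 8.2–9.0% |

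Simulated median shifts were about 0.3 to 0.6 h at 2% versus 3% and 2.1 h at 4% versus 8%. The exact values in the table are preferred. The difference in medians varies between trials with an SD of about 4.0 h.

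**Hospital stay, other assumptions.** Survivors log-normal, median 9 d, log-SD 0.6; deaths at 0.5 to 7 d. Then q = 0.892. At 3% versus 6%, θ = 0.5 − 0.392 × 0.03 = 0.488 as written and 0.515 with death worst; the raw mean is 0.20 d shorter in the arm with more deaths. At 5% versus 10% the simulated figures are 0.481, 0.525 and 0.33 d. The reversal is the same.

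**Day 28.** In the ICU model the share of stays beyond 28 d (672 h) is 1 − Φ(ln(672/48)/0.8) = 0.05%. For hospital stay it is 1 − Φ(ln(28/9)/0.6) = 2.9%, or 7.8% at log-SD 0.8. For a true 13% shortening, capping at 28 d shrinks the simulated mean difference from 1.43 to 1.31 d (log-SD 0.6) or from 1.64 to 1.25 d (log-SD 0.8). Mann-Whitney power stays at 79.6% and goes from 56.0% to 55.9%, since the cap only creates ties at the top.

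**The case against.** The article nowhere says that death is scored as a good result. Section {20a} is a general paragraph that also serves peak creatinine, serum albumin and fluid balance, and an analysis plan not shown may hold a death rule. A reader might infer that the trial has chosen to reward early death; the text does not support that. What stands is narrower: the article does fix the tests and the analysis set, and applied as written they let an early death count as a short stay. A later plan would have to add to or override them.

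The harm is also conditional and visible. It needs a mortality difference, and mortality is reported in the same table. A doubling from 4% to 8%, with every death below the median stay, is near a worst case, and even then the median shift is about half the between-trial SD (2.05 against 4.0 h). At a one-point gap it is lost in noise. This limits the weight of the point but does not remove the misdirection.

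Two further inferences are not supported. One is that the day-28 limit distorts all three outcomes: it is negligible for ICU stay under the model above, no calculation supports it for ventilation time, and for hospital stay a rank test hardly notices it. The other is that the normality and Levene checks are shown to do harm: they form a decision rule stated in advance, and no error was quantified here. They matter because they leave the reported contrast open for outcomes that need a defined one.

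**Conclusion.** The point holds as a cheap improvement of minor to moderate weight. As written, three secondary outcomes count an early death as a favourable value. With equal mortality there is no bias. With unequal mortality the lean is towards the arm with more deaths: about 0.5 h of median ICU stay at 2% versus 3%, about 2.1 h at 4% versus 8%, with wrong-direction significance rising from about 2.5% to between 8% and 9% at the latter. Ranking death worst reverses the direction.

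All mortality and stay inputs are assumptions. The direction needs only that patients who die tend to have shorter stays than survivors (q above 0.5); late deaths after long stays would weaken or reverse it. The day-28 limit is a minor point, mainly for the mean hospital stay. The primary outcome, its analysis and the sample size are not touched.

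**What to change.** For ICU stay, hospital stay and ventilation time only, replace the data-driven choice of test with one rule fixed before the data are analysed by arm. Either version serves:

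- **Rank version.** One Mann-Whitney comparison with in-hospital death ranked worst and patients still in hospital at day 28 ranked at 28 days, just better than death. Report the probability of a worse result with its confidence interval.
- **Time-to-event version.** Time to live ICU discharge, live hospital discharge and end of ventilation alive, with death as a competing event and patients without the event censored at day 28. Compare cumulative incidence; merely censoring deaths in a log-rank test would not count them as failures.

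In both, show survivors' raw medians descriptively, and state that deaths are not missing values for the multiple imputation.

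The cost is wording. Death is already collected under section {13} and no patients are added. End of ventilation may need a definition, including how reintubation counts, if the full protocol has none. The downside is a less familiar summary that mixes duration with mortality, which is why the survivors' medians should stand beside it.

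### Peak creatinine is compared as an absolute value without baseline adjustment, which costs precision (not validity) in the trial's only continuous kidney-function outcome

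*Protocol article*

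**What the plan says.** - **Outcome.** Outcomes {12}, Table 2, lists "Peak SCr (μmol/l" among seven tertiary outcomes. The unit makes it an absolute level. It is the only continuous measure of kidney function in the table. "Initiation of CRRT" is a separate tertiary outcome, and no rule connects the two.
- **Analysis.** Statistical methods {20a} prescribes "Student’s *t* test for continuous variables with equal variance, Welch’s *t* test for continuous variables with unequal variance, and Mann-Whitney *U* test otherwise". It also says "Normality of continuous variables will be assessed and log-transformed where appropriate". No baseline covariate is named.
- **Population.** Eligibility criteria {10} excludes "eGFR < 15 mL/min/1.73 m^2" and sets no upper limit, because type of surgery alone can qualify a patient (for example "Have had a combined valve and coronary procedure").
- **Randomisation.** Sequence generation {16a} stratifies by hospital and by eGFR below or above 60. The subgroup analysis in {20b} uses the same cut.
- **Primary outcome.** AKI in Table 1 is scored mainly against the patient's own baseline creatinine, and starting renal replacement counts as stage III.

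**The concern.** The protocol says its outcomes were picked to capture acute deterioration or recovery. An absolute peak captures level. A patient who goes from 250 to 255 μmol/l has no AKI under Table 1 (a rise of 5, ratio 1.02). One who goes from 80 to 200 within 7 days is stage II (ratio 2.5). Raw peak ranks the first patient as worse.

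Between randomised arms, starting level is noise that albumin cannot influence. A test that ignores it carries that noise in its standard error. At stake is the chance of seeing a moderate effect on the one continuous kidney measure, when the baseline value needed to remove the noise must already be recorded to score Table 1. A log transformation deals with skew and leaves the baseline variance in place.

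A second, smaller matter is that continuous renal replacement therapy (CRRT) clears creatinine. In patients who start it, any further rise may not be seen, and raw peak gives the event itself no weight.

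**Working it through.** **1. The plan's own figure.** The only sample size stated is for AKI: 30% against 20%, two-sided 5%, 80% power, 590 patients. With pooled variance,

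n per arm = [1.960·√(2·0.25·0.75) + 0.842·√(0.30·0.70 + 0.20·0.80)]² / 0.10² = 293.2, so 294 per arm or 588 in total.

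At 295 per arm the power is 80.2%. The figure of 590 reproduces and does not depend on peak creatinine.

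**2. Assumptions.** The protocol gives no creatinine SD, baseline distribution or split between strata. Assumed:
- half the patients in each eGFR stratum;
- median baseline 135 μmol/l (eGFR < 60) and 85 μmol/l (eGFR ≥ 60), with log SD 0.30 and 0.18;
- peak = baseline × ratio, the ratio independent of baseline, with log SD s = 0.2, 0.3 or 0.4.

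**3. Variance of log baseline.**
- Between strata: [ln(135/85)]²/4 = 0.4626²/4 = 0.0535.
- Within strata: (0.30² + 0.18²)/2 = 0.0612.
- Total: 0.1147.

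**4. Share due to baseline, and power.** Var(log peak) = 0.1147 + s². Baseline share = 0.1147/(0.1147 + s²). For a log difference of 0.08 (about 8%) with 295 per arm, power = Φ(0.08/√(2V/295) − 1.96). V is Var(log peak) for the unadjusted comparison and s² for the ratio.

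| s | Var(log peak) | Var(log peak)/s² | Baseline share | Power, peak unadjusted | Power, ratio |
|---|---|---|---|---|---|
| 0.2 | 0.1547 | 3.87 | 74% | 70% | >99% |
| 0.3 | 0.2047 | 2.27 | 56% | 57% | 90% |
| 0.4 | 0.2747 | 1.72 | 42% | 46% | 68% |

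**5. Does stratification already solve this?** Stratified randomisation removes the between-stratum part (0.0535) from the true sampling variance, but an unadjusted test still puts it in the standard error. Power becomes Φ{[0.08 − 1.96·√(2V/295)] / √(2(0.0612 + s²)/295)}, with V = Var(log peak). This gives 74%, 59% and 45%, close to the unadjusted column above. The within-stratum part, 0.0612/0.1147 = 53% of the baseline variance, is untouched by stratification.

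**6. Wider assumptions.** Baseline eGFR was simulated with 30% to 70% of patients below 60 and converted to creatinine for an assumed 70-year-old man with an MDRD-type equation. On that conversion eGFR 15, 30, 45, 60 and 90 correspond to about 352, 193, 136, 106 and 74 μmol/l. With a median ratio of 1.2, baseline explains 78–80% of the variance of peak at s = 0.15, 66–69% at 0.20, 55–58% at 0.25, 46–49% at 0.30, 31–35% at 0.40 and 21–24% at 0.50. The share passes one half between s = 0.25 and 0.30.

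**7. The same loss without an assumed effect.** Let R² be the baseline share. The detectable difference at 80% power is 2.80·√(2/295) = 0.231 SD of peak unadjusted, and 0.231·√(1 − R²) adjusted.

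| R² | Detectable, adjusted (SD) | Unadjusted power where adjusted power is 80% |
|---|---|---|
| 0.3 | 0.193 | 65% |
| 0.5 | 0.163 | 51% |
| 0.7 | 0.126 | 34% |

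**8. CRRT.** No figure can be put on this, because the document gives no CRRT rate.

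**The case against.** The strongest reply is that this is one unpowered tertiary outcome. The primary and stage II/III outcomes are already scored against baseline, and renal replacement counts as stage III in both. Section {20a} is headed for primary and secondary outcomes, so applying it to a tertiary one is an inference. An article may also leave covariate adjustment and the handling of values after CRRT to the full protocol or analysis plan, neither of which is shown. The limited importance stands, and so does the point about CRRT detail. On adjustment, however, the article is not silent: it fixes an absolute unit, and it fixes unadjusted tests for continuous variables in general terms. The suggestion is an improvement on a stated method.

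Three stronger readings are tempting and are not supported:

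- *Raw peak mostly reflects baseline.* That holds for some assumptions and fails for others: the share is 42% at s = 0.4 and about 21% at s = 0.5. The document does not settle it.
- *The comparison is biased.* Allocation is randomised 1:1 and stratified at eGFR 60, so baseline is balanced in expectation. The example of two patients compares individuals, not arms.
- *CRRT artificially lowers the peak.* A maximum already recorded cannot fall. CRRT can only cut off a further rise, in an unknown number of patients. Different use between arms is conceivable, since the trial is open-label and dialysis is at the clinician's discretion, but it would be visible in the separate CRRT outcome.

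**Conclusion.** The point holds as one of efficiency. Under the assumptions in steps 2 to 4, leaving baseline out multiplies the variance by 1.7 to 3.9 and lowers power for an 8% difference from between 68% and over 99% to between 46% and 70%. The size depends on variances that the protocol does not give; the direction does not change anywhere in the range examined. The 8% effect is illustrative, since the trial set no target for this outcome. The CRRT point is a possible truncation of unknown extent. Nothing here touches the primary or secondary conclusions or the 590 patients, so this is a modest but nearly free improvement.

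**What to change.** In the analysis plan, and by a note to Table 2, name one analysis for this outcome: log peak creatinine compared between arms by linear regression, adjusted for log baseline creatinine and eGFR stratum, and reported as a ratio of geometric means with its confidence interval. Using the log peak-to-baseline ratio as the response with the same covariates gives the identical treatment estimate, so either wording will do. Show raw peak in μmol/l descriptively by arm.

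As a separate sensitivity analysis, compare the peak-to-baseline ratio by Mann-Whitney test with patients who start renal replacement ranked worst. Keep it apart from the regression: a worst rank has no value on the log scale, so the two cannot be merged into one analysis.

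The cost is a few sentences. Baseline creatinine and the start of renal replacement are already needed to score Table 1, and no extra patients are required. The small downside is that the treatment effect is a ratio and not a difference in μmol/l.
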